### Data collection

Each participant’s characteristics such as age and body weight as well as ASA grade, durations of DPNB and rigid cystoscopy, VAS scores, vital signs, and the incidence of adverse events during rigid cystoscopy will be recorded in a designed data form by an investigator.

### Sample size

The sample size calculation was based on the primary outcome, the intensity of pain measured on the VAS at cystoscopic inspection of the external sphincter. There are no data regarding VAS score for men when the rigid cystoscope passes through the membranous urethra. We therefore conducted a pilot study to determine the sample size prospectively. Based on our pilot data and literature relevant to pain during male rigid cystoscopy [11], assuming a standard deviation (SD) of 2.6, an α of 0.05, and a power of 90 %, 56 patients in each group are required to demonstrate a clinically relevant difference of 1.6 units in VAS score at cystoscopic inspection of the external sphincter.

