### Statistical analysis

Statistical analysis will be performed with the SPSS (version 18; SPSS Inc., Chicago, IL) and SAS (version 9.3; SAS Inst. Inc., Cary, NC). All statistical tests will be two-sided, and the level of significance will be set at 0.05. Data with a normal distribution will be expressed as mean ± SD and tested by one-way ANOVA with Dunnett’s post hoc test as appropriate. Continuous data without a normal distribution will be expressed as median with interquartile range and analyzed using the MIXED procedure of the SAS statistical program for repeated measures followed by Tukey-Kramer adjustments.

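### The stated 90 % power matches one unadjusted two-group comparison; under the planned Dunnett adjustment, 56 men per arm give about 85 % per comparison

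*Protocol article*

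**What the plan says.** Under Sample size, the protocol article bases the calculation on VAS pain at inspection of the external sphincter. It sets "an α of 0.05" and 90 % power, "assuming a standard deviation (SD) of 2.6". The result is that "56 patients in each group are required to demonstrate a clinically relevant difference of 1.6 units in VAS score". The section does not say which two arms the 1.6 units separate, and it does not mention multiplicity.

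Trial design and Randomization describe three arms allocated 1:1:1, which makes 3 × 56 = 168 men. The Interventions section labels the tetracaine gel arm as the control.

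Under Statistical analysis, "All statistical tests will be two-sided, and the level of significance will be set at 0.05". Normally distributed data are to be "tested by one-way ANOVA with Dunnett’s post hoc test as appropriate". Continuous data that are not normal go to a repeated-measures mixed model "followed by Tukey-Kramer adjustments".

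**The concern.** A difference of 1.6 units is a difference between two arms, so in this plan it is shown by the pairwise step. Both named pairwise procedures use a larger critical value than a single test at 0.05, because they share the 5 % error over two comparisons (Dunnett) or three (Tukey-Kramer). If 56 was obtained without that allowance, the stated 90 % describes a different test from the one that will be run.

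The stake is how a negative result will be read. A non-significant contrast on the primary outcome would be taken to carry a 10 % risk of having missed a 1.6-unit effect. Under the planned adjustment that risk is about 15 % with Dunnett, and about 19 % with Tukey-Kramer under the assumption given in the working.

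**Working it through.** **Inputs.** From Sample size: difference 1.6, SD 2.6, α 0.05, power 90 %, n = 56 per arm. From Statistical analysis: two-sided tests, Dunnett or Tukey-Kramer. From Trial design and Interventions: three arms, with tetracaine gel as control.

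**1. Reproduce the plan's figure.** For two groups, two-sided, no adjustment:

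n = 2 × (1.960 + 1.2816)² × (2.6/1.6)² = 55.49, rounded up to 56.

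The normal-approximation power at 56 is 90.3 %. The article does not name its formula, so the match is an inference. The other routes tried do not give 56:

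| Calculation for 90 % power | n per arm |
|---|---|
| Two-group, two-sided, normal formula | 56 |
| Two-group, two-sided, t test | 57 |
| Two-group, one-sided | 46 |
| Three-arm ANOVA F test, one arm 1.6 apart from the other two | 52 |
| Three-arm ANOVA F test, means 0, 0.8, 1.6 | 68 |
| Dunnett, per comparison | 66 |
| Tukey, three pairs, per comparison | 71 |

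**2. Power of one comparison at 56 per arm.** The standard error of a difference is 2.6 × √(2/56) = 0.491. The noncentrality is 1.6/0.491 = 3.256. The error degrees of freedom are 3 × 56 − 3 = 165. Power is the probability that a noncentral t with these values exceeds the critical value in absolute size:

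| Procedure | Critical absolute t | Power per comparison |
|---|---|---|
| Unadjusted | 1.974 | 89.9 % |
| Dunnett, 2 comparisons with control (correlation 0.5) | 2.231 | 84.6 % |
| Tukey, 3 pairs (studentized range divided by √2) | 2.365 | 81.3 % |

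**3. Power over both Dunnett comparisons.** If both active arms differ from control by 1.6, simulation gives about 94 % for at least one significant comparison and about 75 % for both.

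**4. If a significant F test is required first.** Dunnett power for a 1.6-unit contrast with control becomes about 81 % (means 0, 0.8, 1.6) to 84 % (one arm 1.6 apart from the other two).

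**5. Status of the Tukey figure.** The article assigns Tukey-Kramer to non-normal data in a repeated-measures model. The 81.3 % treats the primary VAS as a single-time-point, normal-theory comparison with SD 2.6, adjusted over three arms. Adjusting over arm-by-time contrasts would lower it, and a precision gain from modelling baseline could recover part of the loss. The article gives no figures for either.

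**The case against.** A reader might infer that the sample-size arithmetic is wrong or that the whole trial is underpowered. The article does not support either reading. The inputs do yield 56, and the section never says that the 90 % applies to each adjusted comparison. Under other definitions of power the figure survives: about 94 % for at least one Dunnett comparison if both active arms differ by 1.6, and 92.6 % for the F test if one arm lies 1.6 from the other two. This stands as a limit on the point, although it depends on the scenario: with means 0, 0.8 and 1.6 the F test has 83 %.

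Nor is there a false-positive problem, since the planned adjustments protect the family-wise error.

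The shortfall is also modest beside the uncertainty in the SD, which rests on a pilot and a literature source not shown. With all else fixed, Dunnett power is about 90 % at an SD of 2.4, while at 2.8 even the unadjusted power is about 85 %. This bears on severity, but the mismatch at the article's own SD remains.

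Finally, this is a condensed article, and the full protocol or SAP may name the primary contrast. That could settle which comparison is meant. It could not make 56 per arm give 90 % for one Dunnett- or Tukey-adjusted comparison in the single-time-point analysis with these inputs.

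**Conclusion.** The point holds per comparison. The 90 % under Sample size fits one unadjusted two-group test. For the adjusted comparisons under Statistical analysis, the power for 1.6 units at 56 per arm is about 85 % with Dunnett, roughly 5 percentage points lower. This assumes SD 2.6, equal arms, all 168 men analysed, and tetracaine gel as the single comparator.

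The Tukey-Kramer value of about 81 % is an approximation under the single-time-point assumption, not the power of the repeated-measures analysis.

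Severity is should-fix. The main pairwise figure stays above 80 %, type I error is controlled and no bias arises, but the article states a power on the primary outcome that its named pairwise tests do not have.

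**What to change.** Keep 168 men and the planned adjustment. In the Sample size section, restate the power as about 85 % for each Dunnett-adjusted comparison with tetracaine gel at a 1.6-unit difference. If Tukey-Kramer may apply to the primary outcome, add about 81 % per comparison and state the single-time-point, normal-theory assumption. Name the comparison, or comparisons, to which the figure refers.

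This takes one or two sentences and no extra patients. The cost is a less favourable stated power.

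Two larger changes are possible but not needed to correct the statement:

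- **More men.** Keeping 90 % per comparison would take 66 per arm with Dunnett (198 in total) or 71 with Tukey (213 in total, same assumption).
- **A fixed testing sequence at 0.05.** This would restore about 90 % for the first contrast. However, the article supports no particular order, a sequence limited to the two contrasts with control would drop DPNB versus combination, and the second contrast would have about 83 % power (both must succeed) if both effects are 1.6.

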### Statistical analysis

Statistical analysis will be performed with the SPSS (version 18; SPSS Inc., Chicago, IL) and SAS (version 9.3; SAS Inst. Inc., Cary, NC). All statistical tests will be two-sided, and the level of significance will be set at 0.05. Data with a normal distribution will be expressed as mean ± SD and tested by one-way ANOVA with Dunnett’s post hoc test as appropriate. Continuous data without a normal distribution will be expressed as median with interquartile range and analyzed using the MIXED procedure of the SAS statistical program for repeated measures followed by Tukey-Kramer adjustments.

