### Randomization

A set of random numbers for the allocation sequence will be generated using a computerized SPSS software package (version 18; SPSS Inc., Chicago, IL, USA). Sealed, opaque assignment envelopes will be used for allocation concealment. The included participants will be randomly enrolled by sealed envelope and assigned to one of three groups (tetracaine gel, DPNB, or combination group) in a ratio of 1:1:1.

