### Outcomes

#### Primary outcome

The primary outcome of this study is intensity of pain measured by a visual analog scale (VAS) at cystoscopic inspection of the external sphincter. VAS is an internationally recognized pain scale with 11 points, ranging from 0 (no pain) to 10 points (maximal pain). Pain can be rated as the following categories: no pain (0 points), mild pain (1–3 points), moderate pain (4–6 points), and severe pain (7–10 points). Participants will be well educated regarding the VAS once enrolled and asked to rate their pain level during the study.

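### A normality check chooses the primary test, and the branch for non-normal data is a normal-theory repeated-measures model with a different set of comparisons

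*Protocol article*

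**What the plan says.** All references are to the protocol article.

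- **Primary outcome section:** the endpoint is defined as follows: "The primary outcome of this study is intensity of pain measured by a visual analog scale (VAS) at cystoscopic inspection of the external sphincter". This is one rating per man at one stage. On the scale: "VAS is an internationally recognized pain scale with 11 points, ranging from 0 (no pain) to 10 points (maximal pain").
- **Statistical analysis, normal data:** "Data with a normal distribution will be expressed as mean ± SD and tested by one-way ANOVA", with Dunnett's post hoc test where appropriate.
- **Statistical analysis, other data:** "Continuous data without a normal distribution will be expressed as median with interquartile range and analyzed using the MIXED procedure" of SAS for repeated measures, followed by Tukey-Kramer.
- **Sample size:** "56 patients in each group are required to demonstrate a clinically relevant difference of 1.6 units in VAS score", which is a difference in means at the external sphincter.

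The section gives no separate rule for the primary outcome. It does not say how normality is judged, or which quantity from the MIXED model would answer the primary question.

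**The concern.** The rule ties two unrelated decisions to one property of the data.

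1. **The remedy does not treat the problem.** PROC MIXED fits a linear model with normally distributed random effects and residuals. Skewed or bounded scores are no reason to turn to it. It estimates means, so the reported summary (median and interquartile range) and the test would describe different things.
2. **The trigger is misplaced.** Whether to model repeated measurements depends on whether the outcome was measured repeatedly. The VAS and vital signs are taken at several stages, but the primary outcome is a single value. As written, a skewed primary VAS goes to a repeated-measures model, while repeated vital signs that look normal do not.
3. **The comparisons move with the branch.** Dunnett makes two comparisons with control. Tukey-Kramer makes all pairwise comparisons. The data decide which family applies to the primary outcome.

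At stake is whether the primary test, its multiplicity adjustment and its contrast are fixed before outcome data are seen. The sample size rests on a mean difference at one stage, and only the normal-data branch clearly tests that.

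**Working it through.** **Inputs.** Difference 1.6, SD 2.6, α 0.05, power 90% and 56 per group (Sample size); two-sided tests (Statistical analysis); three arms "in a ratio of 1:1:1" (Randomization); integer scores from 0 to 10 (Primary outcome). The document does not give the distribution of scores or the arm means, so these are assumed below.

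**Step 1: the plan's own figure.** n per group = 2 × (1.960 + 1.282)² × 2.6² / 1.6² = 55.5, rounded up to 56. The stated figure reproduces. Power at 56 is 90.3% by the normal approximation and 89.8% by the two-sample t-test. This is one unadjusted comparison of means.

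**Step 2: what the branch does to power.** Standard error = 2.6 × √(2/56) = 0.491. Noncentrality = 1.6 / 0.491 = 3.256. Residual df = 3 × 56 − 3 = 165. Power comes from the noncentral t distribution.

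| Comparisons | Critical \|t\| | Power for 1.6 | n per group for 90% |
|---|---|---|---|
| One, unadjusted | 1.974 | 89.9% | 57 |
| Dunnett, two against control | 2.230 | 84.7% | 66 |
| Tukey, three pairs | 2.365 | 81.3% | 71 |

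The switch therefore costs 84.7 − 81.3 = 3.4 percentage points. The Tukey row treats the contrast as a single-stage comparison with 165 df, so it only illustrates the MIXED branch.

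**Step 3: how often the switch would operate.** Scores were simulated with 56 per arm and 2,000 runs per scenario (400 for Lilliefors), as rounded normals clipped to 0-10 (latent SD 2.6) and as rounded beta scores (SD 2.6). Assumed control means were 3 to 6, with both block arms either 1.6 lower or, for control means 3 to 5, equal to control. Tests were at 0.05.

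| Rule | Declared non-normal |
|---|---|
| Shapiro-Wilk, any arm, benefit of 1.6 in both block arms | 86-100% |
| Shapiro-Wilk, any arm, all scenarios | 67-100% |
| Lilliefors, any arm | 88-100% |
| Shapiro-Wilk on pooled residuals | 61-100% |
| Shapiro-Wilk, control arm only | 32-100% |

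The lowest control-arm figures come from clipped normals centred mid-scale: 32% at mean 5 and about 60% at means 4 and 6.

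**Step 4: is leaving ANOVA necessary?** One-way ANOVA on skewed integer scores (beta, mean 3, SD 2.6, 56 per arm, 5,000 runs, no true difference) rejected in 4.8%. In that scenario non-normality gave no reason to abandon it.

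**The case against.** The strongest reply is that the authors probably had the repeated VAS and vital signs in mind for MIXED, since the sentence mentions repeated measures. The primary outcome and sample size are both fixed at the external sphincter, and a sphincter-specific contrast from MIXED would estimate the same mean difference as ANOVA. Dunnett and Tukey each control familywise error within their branch, and all-pairs Tukey still contains both comparisons with control. Much of this stands, and it limits the point. It does not remove it, because the written trigger is non-normality and the primary outcome is not exempted.

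A reader might infer more than the document supports:

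- **That the VAS will almost always be declared non-normal.** No normality test and no pilot distribution are given. Besides the control-arm figures above, a one-sample Kolmogorov-Smirnov test that ignores estimation of mean and SD rejects in any arm in only 6-33% at control means of 4-5, with one arm lower by 1.6. Clipping also shrinks the SD and the difference at low means, so those scenarios match the sample-size assumptions less well.
- **That power could fall to about 37%.** This requires Tukey-Kramer across 21 arm-by-stage means. The document does not say so.
- **That the 1.6-unit effect would be averaged over stages**, to 0.23 or 1.14 units. This requires the arm main effect, baseline included, to be the primary test. The document does not say that either.
- **That one-way ANOVA of repeated outcomes is invalid.** Comparing independent arms at a given stage is valid. It only leaves information unused.
- **That type I error is inflated.** No calculation here shows this for MIXED or for the two-step procedure.

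**Conclusion.** The point holds as a wrongly stated rule that reaches the primary outcome. Three parts rest on the text alone: the trigger is non-normality, the method it triggers is a normal-theory model of means paired with a median summary, and the comparison family changes with the branch. The primary contrast under MIXED is not named.

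The demonstrated size is modest: about 85% against 81% power for 1.6 units, assuming SD 2.6, 56 analysed per arm and a single-stage contrast. How often the switch operates depends on the unstated normality rule and the unknown means. It would often operate (about 86-100% with Shapiro-Wilk in any arm under a benefit in both block arms, about 30-100% under other rules or means, and less still with the uncorrected Kolmogorov-Smirnov test). It should be fixed because the primary test should not depend on that, but the documents do not show that the result would be wrong.

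**What to change.** Reword the Statistical analysis paragraph along these lines:

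1. **Primary analysis, irrespective of any normality test:** a one-way linear model (ANOVA) of VAS at the external sphincter, with Dunnett contrasts of each block arm against tetracaine gel.
2. **Sensitivity analysis:** a rank-based test of the same two comparisons.
3. **DPNB versus combination:** a stated secondary comparison. It is the only one that shows what the gel adds to the block, so it should not vanish with the Tukey-Kramer step.
4. **Repeated VAS and vital signs:** MIXED because they are repeated, with stage-specific contrasts, and means reported alongside the model.

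The cost is one extra sensitivity analysis, and DPNB versus combination lies outside the primary error-controlled family. No new data are needed. The Trial status section says recruitment is under way, and the Blinding section keeps the allocation concealed until the final analysis report, so the rewording can be done before unblinding. The fixed analysis has about 85% power per comparison at 56 per group, not 90%. That follows from the Dunnett adjustment already in the plan, not from this change.

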## Discussion

Cystoscopy plays an important role in both diagnosis and treatment in urology. The rigid cystoscope is still applied in many health care centers because of its lower cost and better optical area and because it is easy to orient compared with flexible devices. However, due to the stiffness of the rigid cystoscope sheath, there is discomfort and even pain resulting from the friction between the wall of the urethra or bladder mucosa and the sheath, and patients sometimes cannot finish the cystoscopy, leading to misdiagnosis or missed diagnosis of the disease [1, 2]. Recently, topical intraurethral lidocaine gel, which is used as a local anesthetic, is most commonly used in clinics to ease the pain of the patients, and this gel also could play a role in lubricating the urethra. However, some reports indicated that pain and discomfort is common in men undergoing rigid cystoscopy even with topical administration of local anesthetic or under general anesthesia [4–6]. Thus, an effective analgesia regimen seems to be urgent for men undergoing rigid cystoscopy.

Men suffer more pain than women in cystoscopy. The most painful part of the procedure for men is when the cystoscope passes through the membranous urethra [7]. Since evidence suggests that some men have DNP branches innervating the membranous urethra and urethra mucosa, could DPNB be effective in relieving the pain for men undergoing rigid cystoscopy, especially when the cystoscope passes through the membranous urethra? To address this question, we designed this trial to evaluate the effectiveness and safety of DPNB for analgesia in men undergoing rigid cystoscopy. The results of this trial may have important implications for exploring the role of DPNB in analgesia for cystoscopy in men.

### Trial status

The trial is currently in recruitment phase. Trial completion is expected by March 2016.

## Abbreviations

ASA: American Society of Anesthesiologists
DNP: dorsal nerve of the penis
DPNB: dorsal penile nerve block
SD: standard deviation
VAS: visual analog scale
